#### 744 **Design aspects that apply to all pilot testing**

745 We hypothesize that providers who utilized individualized, tailored recommendations will find  
746 that they facilitate discussions of preventive care and shared decision-making. We hypothesize  
747 that patients who received individualized, tailored recommendations will change their intentions  
748 around preventive care (which services they intend to do in the next 1 month or 6 months). We

also hypothesize that patients who receive the intervention will report use of shared decision making. We also will interview providers (Figure 6).

**Figure 6.** Sample Questions for Provider Interviews (Draft, Appendix D)

|                                                                        |
|------------------------------------------------------------------------|
| What value did our approach add to the patient encounter?              |
| What was most/least helpful? How could it be improved?                 |
| Did the tool encourage shared decision making with patients? How?      |
| Are you inclined to use the tool in practice? Are there any obstacles? |
| How did it fit with clinical work flow? How might that be improved?    |
| What other information would be helpful?                               |

**Sample Size:** On average, a 1.0 FTE provider sees 8 eligible patients/week; our median FTE is 0.5 (range: 0.2-1.0). As pilot testing, we do not require a pre-specified number of surveys to be completed. (We assume a baseline SDM-Q-9 mean and standard error of 31 and 9, respectively, on a 45 point scale.) An information sheet will be used for providers, and an additional information sheet will also be provided to patients stating that their doctor is participating in a research study. For patients who are interested in providing feedback, the information sheet will also describe the survey. The intervention is minimal risk because providers can ignore individualized recommendations, and providers retain discretion in ordering.

**Rapid Improvement:** Following each burst, the study team will review feedback and identify next steps. As needed, we will spend approx. 1-4 weeks improving use of the decision aid, the quality of shared decision making (from both patient and provider perspectives), and workflow before implementing the next round. Testing will stop after approx. 4 rounds or when feedback suggests that the process cannot be further improved in an exploratory study. The finished product will represent a tailored decision aid ready for wide-scale testing.

**Cognitive interviews:** Selected patients (particularly early in the study) may be asked to participate in cognitive interviews, to help the study team better understand opinions of the individualized preventive care recommendations. Because these interviews are likely to be short (10-15 minutes), the patients who participate in cognitive interviews will not receive additional compensation.

**Survey mechanics:** The surveys will be administered in RedCAP. Patients will be offered the opportunity to complete the survey immediately after their appointment, on a Cleveland Clinic computer. Alternatively, patients who prefer may complete the survey on their own computer, using the internet. In this case, we will provide patients with the web address and a code required by RedCap. This printout will come directly from RedCap, and an example is enclosed. Finally, if patients prefer, we can ask them the survey questions over the phone. Patients will have 3 business days after their appointment to complete the survey. Survey responses will be confidential, not anonymous, in order to allow researchers to know which patients completed the survey for mailing of gift cards. Answers to the survey questions will not be shared with patient's doctors; participants will be informed of confidentiality.

**Data storage:** Cleveland Clinic Center for Value-Based Care Research investigators will collect data as required by the studies discussed within the protocol. Patient data will be stored on site (in a secure REDCap database) and access will be controlled in accordance to Cleveland Clinic and HIPAA standards. Protected Health Information (PHI) will not be shared outside of Cleveland Clinic.

791

## Amendment 5

792

### Patient feedback interview guide

#### 793 Oral feedback

794 Hello [NAME], this is [NAME] calling from Cleveland Clinic. I am calling about a recent  
795 appointment you had with [provider name] Is now a good time?

796 IF NO: When would be a good time? [SCHEDULE APPOINTMENT]

797 Great. You may remember seeing a handout called “How Can You Improve Your Health?”  
798 about preventive care recommendations that were created just for you. Afterwards, you  
799 completed a survey as part of a research study. I would like to ask you feedback about that, so  
800 we can help improve the research for other patients and doctors in the future. The interview  
801 would last about 15 to 30 minutes, and we could do it over the phone now or another time that  
802 would be good for you. If you participate in the interview, we would also mail you another \$25  
803 gift card,

804 Before we get started, I want to say that we take your feedback very seriously. So far, we have  
805 changed the “How Can You Improve Your Health?” materials [NUMBER—currently 8 or 9]  
806 times based on suggestions from other patients and providers. So we are interested in both what  
807 you liked and what you didn’t like. If you loved the research study, great, but if you don’t  
808 remember it or even if you threw it in the garbage, that’s fine too. Those are exactly the kind of  
809 comments we want to hear. Is that ok with you? Great, thank you. Okay, so to get started:

810 [ASK ANY OF THE FOLLOWING QUESTIONS, OR RELATED QUESTIONS, THAT MAY  
811 PROVIDE USEFUL FEEDBACK.]

812 Do you remember seeing the “How Can You Improve Your Health?”  
813 handout/recommendations?

814 Overall, how useful did you find the individualized recommendations?

815 Can you tell me a bit about the conversation (was it different from usual conversations with your  
816 doctor? How so? How was it similar?)

817 What did you think of the recommendations?

818 Do you remember any of the specific recommendations on the handout? Can you tell me more  
819 about what you thought of them? [Study team may remind patients of the recommendations, if  
820 needed.]What do you plan to do with it / what did you do with the recommendations after your  
821 visit?

822 Did you follow any of the recommendations? Which ones?

823 What led you to choose those services instead of others? Was the handout helpful in making that  
824 decision? How?

825 Were there other recommendations that you thought of changing, but didn't? Can you tell me  
826 more about that?

827 Did you believe the recommendations? Can you please tell me more about that? What would  
828 have made them more believable?

829 Did it change your interest at all in preventive care, how so? [Study team may reference  
830 particular recommendations from the individualized recommendations, if needed.]

831 What else would you like to see from individualized recommendations?

832

833 How could we make it better?

834

835 Do you think it would be helpful for other patients?

836

837 Thinking back to your office visit what else was particularly helpful during the visit, how was  
838 that more or less useful than the individualized recommendations, etc.

839

840 Is there anything else you would like to share with us?

841 Thank you for your time. We appreciate your continued participation in the research study.

842

843 **V 8/5/19**

844

845

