
## **Phase II pilot testing**

As Phase I pilot testing winds down, the research team will conduct a subsequent phase of pilot testing that is broader and includes randomization. The protocol for Phase II pilot testing is the same as for Phase I, with the following exceptions:

1. Instead of just physicians, pilot testing may be conducted with any primary care provider (e.g., physicians, physician assistants, nurse practitioners, registered nurses),
2. Pilot testing may be conducted at any Cleveland Clinic internal medicine, community internal medicine, or family medicine department. There is no targeted number of practice sites or providers.

- 707 3. Shortly before each appointment at which the decision aid may be discussed, the visit  
708 will be randomized to “intervention” or “control.” During intervention appointments,  
709 the individualized recommendations will be made available to providers as per Aim  
710 1. During control appointments, the research team may still generate individualized  
711 recommendations but will not make them available to providers. Regardless of  
712 whether the appointment was intervention or control, the patient will still be informed  
713 that their doctor is participating in a research study, and we will ask patients if they  
714 would be interested in providing feedback in the form of a 10-15 minute survey, as  
715 per Aim 1. As with Aim 1, the patient will **not** be required to complete the survey.  
716
- 717 4. Patients who choose to complete the survey will be notified that after their  
718 appointment, we may review their medical record to see which health care services  
719 they receive during the next 1 year. Providers will be similarly notified that we may  
720 review the medical records of their study patients. The purpose of this review is to  
721 see whether provider conversations had an impact on which preventive services were  
722 ultimately provided to patients. To ensure that patients are aware of this, we will only  
723 review the medical records of patients who chose to complete the survey. This  
724 process presents no more than minimal risk of harm to subjects and involves no  
725 procedures for which written consent is normally required outside the research  
726 context.  
727
- 728 5. We will use a different survey from Phase I pilot testing. While Phase I pilot testing  
729 is primarily intended for general feedback on the design of individualized preventive  

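### The Amendment 5 interview calls can remind intervention patients of their recommendations while their one-year service-use window is open, with no matching call to controls

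*Supplement*

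**What the plan says.** **Randomised phase.** Amendment 4, Phase II pilot testing, item 3 randomises each visit. For control visits the team may still generate "recommendations but will not make them available to providers. Regardless of" arm, patients in both groups are told that their doctor is in a study and are offered the same survey.

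**Record review.** Item 4 says that records of survey completers may be examined for the services "they receive during the next 1 year. Providers will be similarly notified that we may" look at records too. The stated purpose is to learn whether the conversation with the provider affected the preventive services delivered. Only survey completers are reviewed.

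**Interview call.** The guide in Amendment 5 (Patient feedback interview guide, Oral feedback) opens: "Hello [NAME], this is [NAME] calling from Cleveland Clinic. I am calling about a recent" appointment. It continues: "Great. You may remember seeing a handout called “How Can You Improve Your Health". It describes the handout as being "about preventive care recommendations that were created just for you. Afterwards, you" (the script goes on) "completed a survey as part of a research study. I would like to ask you feedback about that, so". Staff may restate the recommendations ("about what you thought of them? [Study team may remind patients of the recommendations, if" needed), and a later prompt lets them cite particular ones. They ask "Did you follow any of the recommendations? Which ones", what the patient plans to do or has done with the handout, and which changes were considered but not made. The call takes 15 to 30 minutes.

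**The concern.** Randomisation makes the arms comparable at the visit. It does not protect against a further contact by the research team, made later and in one arm only, that bears directly on the outcome. A 15 to 30 minute talk about a patient's own recommendations, with a possible restatement of them and a question on which were acted on, could plausibly prompt some patients to arrange a service they had let slip. If that happens inside the one-year window, the record review counts it as an effect of the decision aid. The review is meant to isolate the effect of the provider conversation, and the call is not part of that conversation.

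**Working it through.** The plan gives no figure on this point: no number of interviewees, no expected service use and, in Amendment 4, no sample size. The check is therefore mainly a matter of setting the texts side by side.

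1. **Who fits the script?** Patients who saw their individualized handout and then did the survey. In Phase II the recommendations are withheld at control visits, so a randomised patient who fits is an intervention-arm survey completer. Phase I patients also received the handout and a survey offer, so they fit too.
2. **Are these the patients under record review?** For Phase II, yes: the review covers survey completers.
3. **Can the call fall inside the year?** The script speaks of a recent visit and asks about plans still open. No interval is given and nothing defers the call. A call within the year is a strong inference, not a stated fact.
4. **Could Phase II patients be called?** By the amendment log, Amendment 5 is dated 9/11/2019. Amendment 3 (1/31/2018) had already introduced Phase II, and randomised enrolment was formally closed by Amendment 6 (11/30/2020). That log entry adds that nobody was enrolled during the pandemic, so enrolment in practice stopped sooner. When the guide was adopted, recent visits could well have been randomised ones.
5. **Is there a counterpart for controls, or any handling in the analysis?** None is described: no parallel call, exclusion, censoring or sensitivity analysis.
6. **Which outcomes are exposed?** Only service use from records. Shared decision making and intentions come from the survey, due within 3 business days of the visit, and the script treats it as already completed.

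**Illustration of size (every input is an assumption).** Shift in arm difference = share of intervention patients called × rise in uptake among those called.

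| Share called | Rise of 5 points | Rise of 10 points | Rise of 20 points |
|---|---|---|---|
| 10% | 0.5 | 1.0 | 2.0 |
| 25% | 1.25 | 2.5 | 5.0 |
| 50% | 2.5 | 5.0 | 10.0 |

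To see what such a shift does to a test, take 65 per arm and 30% uptake with no true effect of the aid. The 65 is half of the 130 surveys named in the opening protocol text and in Amendment 1; the 30% is an assumption. For a two-sided 5% test of two proportions, the chance of rejecting in favour of the intervention is Φ[(s − 1.96·SE₀)/SE₁], where s is the shift, SE₀ the pooled and SE₁ the unpooled standard error.

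- s = 0.05: SE₀ = √(2 × 0.325 × 0.675/65) = 0.0822 and SE₁ = √[(0.21 + 0.2275)/65] = 0.0820, so Φ(−1.35) ≈ 9%.
- s = 0.10: SE₀ = √(2 × 0.35 × 0.65/65) = 0.0837 and SE₁ = √[(0.21 + 0.24)/65] = 0.0832, so Φ(−0.77) ≈ 22%.
- s = 0.005: about 2.9%.

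The nominal rate in that direction is 2.5%. The effect thus runs from negligible to material, depending on inputs the documents do not supply.

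**The case against.** Much of the case on the other side stands.

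- **Everyone called is a randomised patient.** A reader might infer this, but the documents do not say so. The guide names no phase, and Phase I patients fit the script as well. The gap is that nothing keeps Phase II patients out.
- **The calls come soon after the visit.** The script says only that the visit was recent. It also allows for patients who have forgotten the handout, and it asks some questions in the past tense.
- **The trial would compare aid plus call with nothing.** It would not. Controls have a primary care visit, the same study notice and the same survey offer, and an unknown part of the intervention arm is never called.
- **The bias is large.** No expected service-use effect or base rate is given, so there is nothing to measure it against. The reminder is optional and used only where needed. Amendment 4 already foresees cognitive interviews with selected patients, which suggests a subset.
- **Service use is a minor outcome.** The record review is permissive, and the hypotheses in Amendment 4 concern provider views, intentions and shared decision making. This limits the weight of the point. Still, the review was added with the express aim of detecting an effect on services delivered, so the comparison should be protected.

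Interviewing recipients about the aid is also legitimate in itself. The point concerns only when the call is made and how the service-use analysis treats it.

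**Conclusion.** The point holds in a limited form. Followed as written, the plan allows an extra research contact in the intervention arm alone, within the window of the service-use outcome and with no provision for it in the analysis. Any uptake it prompts biases that comparison in favour of the aid. This rests on two inferences, that Phase II patients are among those called and that calls fall within the year. Both are likely; neither is stated. The size cannot be determined from the documents and may be small: 0.5 to 10 percentage points over the assumed ranges above. The survey outcomes are untouched.

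**What to change.** State in the interview guide which phase the interviewees come from. If Phase II patients are to be called within a year of the visit:

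- choose them at random from intervention-arm survey completers;
- log who was selected, who was reached and the date of each call;
- make the service-use comparison, or a planned sensitivity analysis, without anyone selected for a call. Dropping only those reached would remove the patients who answer the telephone and bring in a selection of its own.

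The cost is one sampling line, a log and some precision. With equal arms and equal variances, leaving out a share f of the intervention arm multiplies the standard error by √{[1/(1 − f) + 1]/2}. That is 1.03 at 10%, 1.08 at 25% and 1.22 at 50%, so the loss is slight unless many patients are selected. The result still applies only to survey completers, a group formed after randomisation, and this change does not cure that.

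Deferring Phase II calls until the record window closes also removes the problem, at the cost of poorer recall. Using Phase I patients only would do so too, but their visits may no longer be recent and they may have seen older versions of the handout.
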